**Exposures**

Prescriptions of gabapentin (Anatomical Therapeutic Chemical code N03AX12) or pregabalin (N03AX16) will be identified in CPRD. The exposed period is defined as the time receiving the medication, calculated with the prescription information in CPRD (daily dosages and quantity prescribed).

The index date is defined as the first date of prescription of gabapentinoid medication. We will calculate the length of exposure using information on prescription date and prescribed days in the database. Patients will contribute to consecutive exposure risk periods while they were continuously exposed to the drug.

**Outcomes**

All-cause drug poisoning, stratified in accidental poisoning and intentional self-poisoning

**Covariates**

Time-varying confounders will include age, seasons, and use of concurrent medications.

Confounding by indication and time invariant factors such as genetic factors, individual vulnerability or psychiatric history are accounted by SCCS as it enables control for both known and unknown confounders that are specific to individual participants and do not vary over time. Each study participant will be used as their own control in this study design.

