**Selection of comparison group**

Included patients will serve as their own control in this study design.^26^ Eligibility will be assessed based on the inclusion and exclusion criteria outlined in the section “Definition of the Study population”. The major advantage of SCCS over the classic design is that it controls for potential effects of measured and unmeasured time-invariant confounders that vary between individuals (i.e. genetic factors, disease severity, and socioeconomic factors).

A 90 days pre-exposure period will be included into the study. Calculation of the IRR during this period of time will be performed to evaluate whether outcomes of interest were caused by the conditions that gabapentinoids prescribed for instead of the use of gabapentinoids, which in turn may introduce bias into the risk estimate during treatment.

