**Sample size consideration**

With an estimated IRR=1.5, n=484 is required with 5% level of significance and 80% power.^30^ The above sample sizes will be enough to study the outcomes with an incidence as low as 0.1%.

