A series of sensitivity analyses will be performed, including a spline-based self-controlled case series analysis, exclusion of patients who died within 6 months of the event, starting follow-up from the first neuropathic or chronic pain diagnosis, restricting to individuals with at least two gabapentinoid prescriptions, varying the length of the pre-treatment period, adjusting only for age and season, extending treatment periods. Self-controlled case series extensions analyses will also be conducted.^34^ A negative control analysis will be performed to explore residual confounding. An additional case-case-time-control analysis^35^ is to validate the main findings, in which the 30 days before the event served as the hazard period and were compared with four randomly selected 30-day reference periods 61 to 180 days earlier, future cases occurring 180 to 360 days later were matched by age, sex, and ethnicity, and adjusted odds ratios (aORs) were estimated using conditional logistic regression. A two-sided significance level of 5% was used for all analyses.

For data analysis, we will utilise either the Statistical Analysis System (SAS) or R programming software.

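### The protocol says SCCS accounts for confounding by indication, but SCCS removes only what stays constant within a person; indication and severity that change over time remain possible confounders

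*Protocol*

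**What the plan says.** The Covariates section states that "Confounding by indication and time invariant factors such as genetic factors, individual vulnerability or psychiatric history are accounted by SCCS". The reason it gives covers confounders that are specific to the person and constant over time. Selection of comparison group repeats the claim, with examples: "i.e. genetic factors, disease severity, and socioeconomic factors".

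The next paragraph of that section adds a 90-day pre-exposure period. Its IRR is meant "to evaluate whether outcomes of interest were caused by the conditions that gabapentinoids prescribed for instead of the use of gabapentinoids", and the paragraph accepts that the treated condition could bias the on-treatment estimate.

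The main model adjusts for age in 1-year bands, season and other concurrent medication. The sensitivity analyses under Statistical Analysis include "starting follow-up from the first neuropathic or chronic pain diagnosis", pre-treatment periods of other lengths, spline-based SCCS and SCCS extensions. A negative control analysis and a case-case-time-control analysis are also planned.

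**The concern.** The indications named under Statistical Analysis include neuropathic pain, postherpetic neuralgia, generalised anxiety disorder, insomnia and bipolar disorder. These can begin, worsen or remit within a window that may span 11 calendar years (1 January 2010 to 31 December 2020), and prescribing follows from them. Unexposed time before onset is then not comparable with exposed time in the same person, and within-person comparison does not repair this.

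If the design is credited with handling indication, a raised IRR is easily read as a drug effect. The Hypothesis section predicts a raised risk, which is also the direction this bias would take if the indication itself raises the risk of poisoning.

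**Working it through.** **1. The text against itself.** Covariates puts confounding by indication among the things SCCS handles, for a reason that covers only constant factors. The pre-exposure paragraph plans a test for bias from the indication. If the first statement held without qualification, the test would not be needed. Psychiatric history and severity are mixed: their stable, between-person part cancels, but episodes and worsening during follow-up do not.

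**2. The protocol's planning figure.** Sample size consideration states: "With an estimated IRR=1.5, n=484 is required with 5% level of significance and 80% power". The exposed share of observation time, r, is not given. Using the signed-root likelihood-ratio formula for SCCS, with ρ = 1.5, a two-sided 5% level and r = 0.09 (assumed):

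- p = ρr/(ρr + 1 − r) = 0.135/1.045 = 0.1292
- A = 2[p ln ρ − ln(ρr + 1 − r)] = 0.01673
- B = (ln ρ)² p(1 − p)/A = 1.106
- n = (1.960 + 0.842√B)²/A = 484

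Other shares give 817 (r = 0.05), 443 (0.10), 263 (0.20) and 194 (0.50). The figure of 484 is consistent with a standard formula and is not in dispute. The value 1.5 is a planning assumption, not a decision threshold.

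**3. Closed form under no drug effect.** Let m be the rate multiplier while the indication is active, and p1 and p0 the shares of exposed and reference time in which it is active. Then

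apparent IRR = [1 + p1(m − 1)] / [1 + p0(m − 1)].

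- m = 2, p1 = 0.50, p0 = 0: 1.50/1.00 = 1.5
- m = 3, p1 = 0.25, p0 = 0: 1.50/1.00 = 1.5
- m = 2, p1 = 0.65, p0 = 0.10: 1.65/1.10 = 1.5
- m = 2, a 90-day flare in a 365-day exposure, p0 = 0: 1 + 90/365 = 1.25
- m = 2, a 30-day flare in a 365-day exposure, p0 = 0: 1 + 30/365 = 1.08

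**4. Simulation under no drug effect.** Assumed inputs: 400,000 persons with one event each, 2,920 days of observation, uniform onset of the indication, exponential lag to treatment (mean 60 days), exponential treatment length (mean 365 days), and risk multiplied by m from onset. The conditional SCCS likelihood was fitted without age, season or co-medication terms. Repeat runs differ by up to about 0.03.

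| On-treatment IRR | m = 1.5 | m = 2 | m = 3 |
|---|---|---|---|
| Persists, no pre-exposure term | 1.24 | 1.43 | 1.73 |
| Persists, 90-day term | 1.24 | 1.43 | 1.74 |
| Persists, mean lag 365 days, no term | 1.21 | 1.38 | 1.60 |
| Resolves with treatment, no term | 1.48 | 1.94 | 2.86 |
| Resolves with treatment, 90-day term | 1.50 | 1.99 | 2.97 |
| Follow-up from onset, persists | 0.99 | 1.00 | 1.00 |
| Follow-up from onset, resolves, no term | 1.38 | 1.75 | 2.41 |
| Follow-up from onset, resolves, 90-day term | 1.49 | 1.97 | 2.91 |

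**5. What the pre-exposure IRR shows.** In the persistent case it is only 1.06, 1.10 and 1.16, which could falsely reassure. In the resolving case it is 1.25, 1.51 and 2.01, below the on-treatment values of 1.50, 1.99 and 2.97, although the drug does nothing. In a separate simulation (484 cases, 365-day exposure, 300 runs), a doubling of risk that starts on the prescription date and lasts half the exposed time gives an exposed IRR of 1.50 and a pre-exposure IRR of about 0.94.

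**The case against.** The strongest reply is that the Covariates sentence rests on factors that do not change, that stable psychiatric history and severity are indeed controlled, and that the protocol already looks for the problem. It plans a pre-exposure IRR, pre-treatment periods of other lengths, follow-up from pain diagnosis, a negative control aimed at residual confounding, and a case-case-time-control analysis whose reference periods lie only 61 to 180 days earlier. The ranking of such analyses may also sit in a statistical analysis plan that is not shown.

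Most of this stands. A reader might infer that time-varying indication is ignored altogether, and the documents do not support that. The same holds for deleting psychiatric history and severity outright: qualifying them is enough. But planned checks do not make the statement about the design true. The pain-anchored analysis also does not reach anxiety, insomnia or bipolar disorder.

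The magnitude is open to challenge too. The protocol gives no multiplier, lag, treatment length or persistence, and the simulation leaves out the planned covariates. A reader might infer that confounding alone will yield 1.5. That does not follow: in the persistent case multipliers of 1.5 and 2 give only 1.24 and 1.43, and short flares give 1.08 to 1.25.

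**Conclusion.** The point holds as a misstatement of a design property. The claim about indication is too broad and conflicts with the protocol's own pre-exposure paragraph. Under assumed multipliers of 1.5 to 3 and no drug effect, the on-treatment IRR is about 1.2 to 1.7 if the indication persists and 1.5 to 3.0 if it resolves with treatment, with or without the 90-day term. These figures show what is possible under stated assumptions. They do not predict the bias in this study.

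A reader might also infer that a drug effect is established once the onset-anchored IRR excludes 1 and the on-treatment IRR exceeds the pre-exposure IRR. The results do not support such a rule. Starting at onset removes the bias only when the indication persists. When it resolves with treatment, both conditions can be met with no drug effect.

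**What to change.** - In Covariates, remove confounding by indication from the factors said to be controlled, and limit psychiatric history to its stable, between-person part. Limit disease severity in the same way in Selection of comparison group.
- State that time-varying indication and severity remain possible confounders, and that age, season and concurrent medication capture them at most in part.
- Extend the planned analysis starting at the first pain diagnosis to other recorded indications, such as anxiety. Report it beside the main IRR, together with the pre-exposure IRR, the negative control and the case-case-time-control results.
- State that a raised main IRR will not be read as a drug effect unless these checks agree. State also that agreement is a safeguard and not proof, because neither onset-anchoring nor the comparison of on-treatment with pre-exposure IRR removes the bias when the indication resolves with treatment.

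The cost is a change of text and an extension of an analysis already planned. The indication-anchored analysis will have fewer cases and less unexposed time, and the conclusion will be more cautious.

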**Selection of comparison group**

Included patients will serve as their own control in this study design.^26^ Eligibility will be assessed based on the inclusion and exclusion criteria outlined in the section “Definition of the Study population”. The major advantage of SCCS over the classic design is that it controls for potential effects of measured and unmeasured time-invariant confounders that vary between individuals (i.e. genetic factors, disease severity, and socioeconomic factors).

A 90 days pre-exposure period will be included into the study. Calculation of the IRR during this period of time will be performed to evaluate whether outcomes of interest were caused by the conditions that gabapentinoids prescribed for instead of the use of gabapentinoids, which in turn may introduce bias into the risk estimate during treatment.

**Sample size consideration**

With an estimated IRR=1.5, n=484 is required with 5% level of significance and 80% power.^30^ The above sample sizes will be enough to study the outcomes with an incidence as low as 0.1%.

**Feasibility count**

The preliminary count in the CPRD contains records of 778,080 and 419,387 individuals with prescriptions of gabapentin and pregabalin, respectively.^31^ Together, more than 1,197,000 patients within CPRD will be eligible for the proposed study. As patients who have taken gabapentinoids will be subjects of interest, almost 1.2 million patients included in the database will be eligible for the overall cohort.

Previous study shows that 1 in 15 has attempted suicide in the UK.^32^ That will be equivalent to 80,000 patients within the cohort having this outcome of interest.

Another previous study shows that 8.9%, 6.3% and 36.7% of patients had unintentional overdose, road traffic incident and head/ body injuries, if they were on gabapentinoids, which will be equivalent to 106,000, 75,600 and 440,400 patients, respectively.^20^

**Statistical Analysis**

Gabapentinoid usage is diverse with multiple indications. It can be prescribed for neuropathic pain, fibromyalgia, postherpetic neuralgia, restless legs syndrome, generalised anxiety disorder, menopausal symptoms, complications of multiple sclerosis, insomnia and bipolar disorder.^2,13-16,19^ There is no other way to estimate their effects for a particular group of patient without using a stratified analysis. SCCS is a method of estimation that focuses on individuals and does not necessitate separate control groups.^33^ As a result, it is considered self-controlled, effectively eliminating the influence of time-invariant factors and we should not include time-invariant factors into the SCCS analysis.

In our study, we will determine the duration of exposure during the study period and compute the incidence rates for the specific outcomes of interest within each exposure risk period. To assess the association between gabapentinoid use and the risk of these outcomes, we will employ conditional Poisson regression. Conditional Poisson regression analysis will enable us to calculate incidence rate ratios (IRRs) by comparing the periods of exposure to gabapentinoids with unexposed periods, adjusted for age in 1-year bands, seasonal effect, and other concurrent medications. Adjusted IRRs, along with their corresponding 95% confidence intervals (CIs), will be estimated for the overall exposure as well as for each predefined exposure risk period. All statistical analyses will be conducted with a significance level of 5%. The calculated IRRs will be stratified by age, sex, ethnicity, types of gabapentinoids, dosage levels and pre-existing comorbidities.

In additional analyses, the interaction between gabapentinoids and opioids or benzodiazepines by comparing the incidence of all-cause drug poisoning across combined exposure windows with periods unexposed to either medication will be examined. Gabapentin-only compared with pregabalin-only treatment periods among individuals who received both drugs during follow-up will also be evaluated.

A series of sensitivity analyses will be performed, including a spline-based self-controlled case series analysis, exclusion of patients who died within 6 months of the event, starting follow-up from the first neuropathic or chronic pain diagnosis, restricting to individuals with at least two gabapentinoid prescriptions, varying the length of the pre-treatment period, adjusting only for age and season, extending treatment periods. Self-controlled case series extensions analyses will also be conducted.^34^ A negative control analysis will be performed to explore residual confounding. An additional case-case-time-control analysis^35^ is to validate the main findings, in which the 30 days before the event served as the hazard period and were compared with four randomly selected 30-day reference periods 61 to 180 days earlier, future cases occurring 180 to 360 days later were matched by age, sex, and ethnicity, and adjusted odds ratios (aORs) were estimated using conditional logistic regression. A two-sided significance level of 5% was used for all analyses.

For data analysis, we will utilise either the Statistical Analysis System (SAS) or R programming software.

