**Methods**

**Study design**

We will apply the self-controlled case series (SCCS) study design in the proposed study.^25^ The analysis will be conducted on a population of individuals who had experienced both the outcome(s) and exposure of interest, which will be prescription of gabapentinoids. Incidence rate ratios (IRRs) will be calculated by comparing the event rates during periods of gabapentinoid exposure to the rates during all other observed time periods, in other words without gabapentinoid exposure. This will be accomplished using conditional Poisson regression.

This design has a significant advantage over the classical cohort design as included participants will act as their own control and it consequently addresses all potential time-invariant confounding effects that vary between individuals, such as genetic factors and socioeconomic factors.^26^ Additionally, we will account for time-varying factors, such as age and season, which can influence the prescription of gabapentinoids. We will also adjust for the concurrent use of other medications as time-varying factors. Sub-group analysis will also be performed for patients who suffer from mental illnesses, type 2 diabetes or cardiovascular diseases.

This method can investigate associations between acute outcomes and transient exposures^26^ and has been used extensively in literatures studying the safety of psychotropic medications and outcomes such as suicide attempts, self-harm and risk of seizure.^20,27-29^

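### The protocol wrongly says that stratifying is the only way to study patient subgroups in an SCCS, and names no heterogeneity test for age, sex, ethnicity or comorbidity

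*Protocol*

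**What the plan says.** The Statistical Analysis section of the protocol notes that gabapentinoids have many indications and concludes: "There is no other way to estimate their effects for a particular group of patient without using a stratified analysis". It then explains that the design is self-controlled and ends that explanation with "we should not include time-invariant factors into the SCCS analysis".

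The next paragraph sets out the strata: "The calculated IRRs will be stratified by age, sex, ethnicity, types of gabapentinoids, dosage levels and pre-existing comorbidities". The Study design section adds: "Sub-group analysis will also be performed for patients who suffer from mental illnesses, type 2 diabetes or cardiovascular diseases". These three diseases probably belong to the comorbidity strata and are not counted here as further factors.

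One error level covers everything: "A two-sided significance level of 5% was used for all analyses". Adjusted IRRs are to be given with 95% confidence intervals.

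Two direct comparisons are planned in the same section. One sets gabapentin-only against pregabalin-only periods in people who received both drugs. The other is an interaction analysis with opioids or benzodiazepines. No comparable test is named for age, sex, ethnicity or comorbidity.

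**The concern.** A stratified IRR answers whether exposure is associated with poisoning within one group. Whether the association differs between groups is a separate question and needs a contrast between the strata. By saying that nothing but stratification is available, the protocol steers the analyst away from that contrast, although the SCCS model supplies it.

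What is at stake is the reading of the subgroup table. Whether a stratum reaches significance depends heavily on how many cases it holds. If the true IRR is the same everywhere, a large stratum may be clearly significant while a small one, such as a minority ethnic group or an uncommon comorbidity, is not. In a study of drug poisoning, the small group could then be taken to carry no added risk. The overall IRR is not affected.

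**Working it through.** **1. Is the statement about stratification correct?** Let person *i* have fixed factor x_i, and let interval *k* have length t_ik and exposure e_ik (0 or 1). Leave out age, season and co-medication terms for brevity. The Poisson rate is

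λ_ik = exp(φ_i + γ·x_i + β·e_ik + δ·e_ik·x_i).

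Conditioning on the person's total number of events, the probability that an event falls in interval *k* is

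t_ik·exp(β·e_ik + δ·e_ik·x_i) / Σ_m t_im·exp(β·e_im + δ·e_im·x_i).

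The terms φ_i and γ·x_i are the same in every interval and cancel. That is the sense in which fixed factors drop out. The term δ·e_ik·x_i changes with exposure and stays. For a two-level factor the IRRs are exp(β) and exp(β+δ), and δ = 0 is the hypothesis of equal IRRs. One model therefore gives the subgroup IRRs and the test of their difference.

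**2. The planned size.** The protocol's Sample size consideration gives "With an estimated IRR=1.5, n=484 is required with 5% level of significance and 80% power". This figure can be neither confirmed nor refuted, because the exposed share of observation time is not stated. The two-sided signed-root likelihood-ratio formula gives 817 cases at 5% exposed time, 443 at 10%, and 484 at about 9.0%. The steps below use only the protocol's own statement that 484 cases give 80% power at IRR 1.5.

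**3. Power within a stratum when the IRR is 1.5 everywhere.** For a stratum with share *s* of *N* total cases, by normal approximation,

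power = Φ(2.802·√(s·N/484) − 1.960), where 2.802 = 1.960 + 0.842.

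The values of *N* are:
- 484, the stated requirement.
- 1,200, which is 0.1% (the lowest incidence named under Sample size consideration) of about 1.2 million patients.
- 4,840, ten times the requirement.
- 80,000, the suicide-attempt projection under Feasibility count. The same section projects 106,000 unintentional overdoses.

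For s = 0.10:

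| Total cases | 2.802·√(0.10·N/484) | Power, 10% stratum | Power, other 90% | One significant, the other not |
|---|---|---|---|---|
| 484 | 0.886 | 0.14 | 0.76 | 0.69 |
| 1,200 | 1.395 | 0.29 | 0.99 | 0.71 |
| 4,840 | 2.802 | 0.80 | 1.00 | 0.20 |
| 80,000 | 11.39 | 1.00 | 1.00 | 0.00 |

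The last column is p(1−q) + q(1−p), with *p* and *q* the two powers.

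**4. Smaller strata.** The same formula gives a 5% stratum power of 0.52 at 5,000 cases and 0.98 at 20,000. A 1% stratum has 0.44 at 20,000 and 0.95 at 80,000.

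**5. The interaction test by comparison.** A simulation with one exposed and one unexposed period per case, 9% exposed time (an assumption) and a common IRR of 1.5 gave a likelihood-ratio heterogeneity test that rejected 5.0% to 5.4% of the time. It covered 50/50, 80/20 and 90/10 splits at 484, 1,200 and 4,840 cases. Its error rate does not depend on how unequal the strata are.

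**The case against.** **No rule of reading significance stratum by stratum is stated.** A reader might infer that the protocol will declare subgroup differences from which strata reach p<0.05. It says only that IRRs will be stratified and given with confidence intervals, and a heterogeneity test can be formed from disjoint strata. This stands. The point is a risk left open.

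**The clause on fixed factors may concern confounding only.** In context it closes a sentence on removing fixed confounders, and there it is right. The plan also stratifies by sex and ethnicity, so it cannot mean that such factors play no part. A reader might infer that the clause forbids interaction terms, but the text does not go that far. Even so, its unqualified wording beside the claim that no other method exists invites that reading and should be limited.

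**Case numbers may be large.** The 484 is a requirement, not a forecast, and the projections are roughly 165 to 219 times larger (80,000/484 and 106,000/484). This stands and removes the problem for all but very small strata if the projections hold. They are rough and made before exclusions, and splitting poisoning into accidental and intentional reduces the cases per analysis.

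**Multiplicity.** A reader might infer an uncontrolled family-wise error rate from the flat 5% level. The number of strata is not given, so any such rate would rest on assumed counts. Adjustment and exploratory labelling of secondary subgroups are commonly left to a SAP, and none is shown here. That argument is not relied on.

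**Direct comparisons already planned.** Drug type and opioid or benzodiazepine co-use have their own analyses, so the point does not extend to them.

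**Conclusion.** The point holds in a limited form. The claim that stratification is the only route is a methodological error on the page. It is not a detail left to a SAP, since a SAP that added the interaction test would be at odds with the protocol's statement. The exclusion of fixed factors is correct for main effects only. For age, sex, ethnicity and comorbidity, separate stratum IRRs are the only stated basis for comparison.

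The size depends on cases per stratum, which the protocol does not give. Under a common IRR of 1.5, a 10% stratum would miss significance about 86% of the time at 484 cases, 71% at 1,200 and 20% at 4,840, and almost never at the projected numbers. The consequence is therefore confined to small strata and rare outcomes. These figures assume that 484 cases give 80% power, that strata share the same exposure pattern, and that the normal approximation is adequate. The error in the text does not depend on them.

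**What to change.** In the protocol's Statistical Analysis section:

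- Delete the sentence claiming that no alternative to stratification exists, or replace it with a statement that subgroup IRRs can come from strata or from exposure-by-factor terms in one conditional Poisson model.
- Limit the exclusion of time-invariant factors to their main effects.
- For age group, sex, ethnicity and each comorbidity, add an exposure-by-factor term, or an equivalent heterogeneity test on the disjoint stratum estimates. Report one heterogeneity p-value per factor beside the stratum IRRs and confidence intervals.
- State that a difference between subgroups will be claimed only on that test, not on which strata are significant.

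The drug-type comparison and the opioid/benzodiazepine interaction analysis can stay as they are.

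The cost is some wording and a small amount of extra analysis on data already held. The downside is that interaction tests have low power, so fewer subgroup differences can be claimed. A non-significant heterogeneity test should not be reported as proof that the groups are alike.

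### The planned opioid/benzodiazepine interaction analysis contrasts both drugs with neither, which estimates a joint effect and not the interaction

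*Protocol*

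**What the plan says.** The Protocol's Statistical Analysis section sets out the main model, a conditional Poisson regression giving IRRs for gabapentinoid-exposed against unexposed time, "adjusted for age in 1-year bands, seasonal effect, and other concurrent medications". It then adds a secondary question: "In additional analyses, the interaction between gabapentinoids and opioids or benzodiazepines" is to be examined "by comparing the incidence of all-cause drug poisoning across combined exposure windows with periods unexposed to either medication". Target and method stand in the same sentence.

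For this analysis the text names no gabapentinoid-only window, no co-drug-only window, no product term, and no ratio or difference of IRRs. The next sentence does name single-drug periods, but for a different question, gabapentin against pregabalin.

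The only effect size in the Protocol is in Sample size consideration: "With an estimated IRR=1.5, n=484 is required with 5% level of significance and 80% power". The Hypothesis section expects a raised risk during gabapentinoid exposure.

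**The concern.** An interaction asks whether the two drugs together do more, or less, than their separate effects would predict. Answering it needs the separate effects. A comparison of both drugs with neither contains those effects as well as any interaction, so a value above 1 may reflect the gabapentinoid alone, the opioid or benzodiazepine alone, the two combining without interaction, or a true interaction.

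At stake is the question this analysis invites: whether adding a gabapentinoid to an opioid or benzodiazepine changes the risk of poisoning. The stated contrast cannot answer it in either direction.

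**Working it through.** **Notation.** All IRRs are against time on neither drug: IRR10 is gabapentinoid only, IRR01 is co-drug (opioid or benzodiazepine) only, IRR11 is both. The multiplicative interaction ratio is θ = IRR11 / (IRR10 x IRR01).

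**Inputs.**
- IRR10 = 1.5: Protocol, Sample size consideration.
- Two-sided 5% level: Protocol, Statistical Analysis ("A two-sided significance level of 5% was used for all analyses").
- IRR01: not in the Protocol. Assumed, shown from 1.0 to 3.0.
- Shares of observation time: not in the Protocol. One assumed scenario for the simulation: neither 60%, gabapentinoid only 10%, co-drug only 20%, both 10%.

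**The plan's own figure.** No number is given for the interaction analysis. The stated n = 484 belongs to the main analysis. The signed-root likelihood-ratio formula for this design without age effects is n = (z_α + z_β√B)² / A, with D = 1.5r + 1 − r, A = 2[(1.5r/D) ln 1.5 − ln D] and B = (ln 1.5)² x 1.5r(1 − r) / (A D²). It needs the exposed fraction r, which is not given. It returns 817 at r = 0.05, 484 at r = 0.09, 443 at r = 0.10 and 262 at r = 0.20. The figure is therefore plausible but cannot be confirmed, and the point below does not depend on it.

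**What the stated contrast estimates.** Rearranging the definition of θ, both versus neither is IRR11 = IRR10 x IRR01 x θ. With no multiplicative interaction (θ = 1) it is IRR10 x IRR01. With no additive interaction it is IRR10 + IRR01 − 1.

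| IRR10 | IRR01 (assumed) | Both vs neither, θ = 1 | Both vs neither, exact additivity |
|---|---|---|---|
| 1.5 | 1.0 | 1.5 | 1.5 |
| 1.5 | 1.25 | 1.875 | 1.75 |
| 1.5 | 1.5 | 2.25 | 2.0 |
| 1.5 | 2.0 | 3.0 | 2.5 |
| 1.5 | 3.0 | 4.5 | 3.5 |
| 1.0 | 2.0 | 2.0 | 2.0 |
| 1.0 | 1.0 | 1.0 | 1.0 |

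The first row shows that the Protocol's own 1.5 is enough: a co-drug with no effect and no interaction still gives 1.5. The sixth row is the reverse: a gabapentinoid with no effect gives 2.0. In the last row neither drug acts and the contrast is correctly 1.

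**How often this would be significant.** Case counts were simulated over the four states with the assumed time shares, 484 cases, 20,000 replicates, and no multiplicative interaction. Tests were Wald tests on the log ratios, without age, season or other adjustment.

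| IRR10, IRR01 | Both vs neither significant | Test of θ = 1 significant |
|---|---|---|
| 1.5, 1.0 | 82% | 5% |
| 1.0, 1.5 | 80% | 5% |
| 1.5, 1.5 | about 100% | 5% |
| 1.5, 2.0 | 100% | 5% |
| 1.0, 1.0 | 5% | 5% |

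**The opposite error.** Take IRR10 = IRR01 = 1.5 and θ = 1/2.25 = 0.44. Then IRR11 = 1.5 x 1.5 x 0.44 = 1.0. With 5,000 cases, both versus neither is significant in 5% of replicates, while the test of θ = 1 detects the interaction in essentially all.

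**Precision of the proper contrast.** The variance of log IRR11 is about 1/n11 + 1/n00, where n is the case count in a state; that of log θ adds 1/n10 + 1/n01. With 484 cases, the same time shares, IRRs 1.5 and 2.0 and θ = 1, the weights are 0.60, 0.15, 0.40 and 0.30 (sum 1.45). Expected cases are then about 200 (neither), 50 (gabapentinoid only), 134 (co-drug only) and 100 (both). The standard errors are √(1/100 + 1/200) = 0.12 and √(1/100 + 1/200 + 1/50 + 1/134) = 0.21, so the interval for θ is about 1.7 times as wide on the log scale.

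**The case against.** The best reply is about reading. The plural windows, and the word used to compare across them, could mean a cross-classification into gabapentinoid only, co-drug only and both, each referred to time on neither. That would be the four-state model recommended below. The reading is possible, though the plural may only reflect that there are two co-drug classes. It does not settle the matter: the single-drug windows are not stated, and three IRRs against a common reference are not an interaction until they are combined.

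A second reply is that coding and derived contrasts belong in a statistical analysis plan. That holds for much of the detail. But the Protocol does not leave the method open; it states one, and that method does not measure the quantity named. A plan that followed the sentence faithfully would carry the mismatch forward.

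A third is that the sizes rest on assumptions. That is correct for the co-drug IRRs, the time shares and the 0.44 scenario. They illustrate the algebra and do not estimate bias in this study. The identity itself does not depend on the time shares.

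It also stands that an IRR for both versus neither is a legitimate quantity under its proper name.

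**Conclusion.** The point holds for the sentence as written: the analysis is called an interaction but defined as a joint effect. Where at least one drug has a non-null effect, as the Protocol hypothesises for gabapentinoids, the contrast generally departs from 1 without any interaction: to 1.5 if the co-drug does nothing, and to 3.0 if its IRR is an assumed 2.0. It can also sit at 1 when an interaction exists.

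Three stronger conclusions might be inferred and are not supported:
- That the contrast always shows a spurious interaction. It does not if both drugs are null.
- That a raised IRR will be reported as an interaction. The Protocol says only that the interaction will be examined and gives no decision rule.
- That the study's main result is compromised. This is an additional analysis with no sample size tied to it, and the main exposed-versus-unexposed IRR is untouched.

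It is a should-fix for a secondary analysis.

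**What to change.** Replace the sentence with a definition along these lines: for opioids and for benzodiazepines separately, fit one self-controlled case series model with four mutually exclusive time-varying states (neither, gabapentinoid only, co-drug only, both). Report IRR10, IRR01 and IRR11 against neither, and define the interaction as IRR11/(IRR10 x IRR01) with its 95% CI.

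The co-drug that defines the states should not also enter that model as a concurrent-medication covariate. The Protocol does not list those covariates, so this should be stated. If coded on the same windows, the covariate would equal the sum of the co-drug-only and both indicators, and the model could not separate them.

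The additive measure IRR11 − IRR10 − IRR01 + 1, and both versus co-drug only as the effect of adding a gabapentinoid, are useful but optional.

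If the team prefers to keep the contrast as it stands, it should be relabelled as the joint effect and no interaction claim drawn from it.

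The cost is a short wording change and a recoded exposure variable, with no new data. The real price is precision: the interaction interval is wider than the joint-effect interval, about 1.7 times on the log scale in the assumed scenario above.
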